## Objectives

We designed the Muva physical activity intervention for people with SMI to improve their social functioning. The intervention focuses on increasing physical activity by implementing group sports activities, active weekly meetings with mental health workers, and a serious game to set physical activity goals. The intervention aims to decrease barriers to physical activity through active involvement of the mental health worker, supporting lifestyle courses, and a medication review.

We will investigate if social functioning and mental and physical health of patients can improve through this package of interventions. We hypothesize that social functioning and quality of life will improve, psychiatric symptoms will decrease, and physical health will improve with an increase in cardiorespiratory fitness, and a decrease in movement disturbances and cardiometabolic disease risk factors.

To gain understanding on movement disturbance severity and the impact on motor execution in SMI, the Sint Hans Rating Scale and gait analysis with markerless motion capture will be performed during the physical measurements in the UMCU. The obtained results may provide new information on which specific movement interventions are recommendable for a better and sustainable implementation of physical activities for people with SMI in the future.

Moreover, we will examine if the lifestyle habits and/or personality type of the mental health worker are associated with the outcomes. Our hypothesis is that mental health workers with healthier lifestyles and a conscious personality type can contribute more to an active and healthy lifestyle of their patients since they might value physical activity as important and are able to consciously plan physical activities and oversee barriers for patients. In addition, we aim to evaluate the barriers and facilitators of the implementation of the intervention by conducting semi-structured interviews with location managers and mental health workers.

This paper aims to describe the Muva study in detail according to the SPIRIT statement [39].

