**Table 1 Tab1:**
[figure not shown]
Design of the pragmatic stepped wedge cluster randomized controlled trial. Control period marked light blue, transition period marked dark blue, and intervention period marked intermediated blue. Time in months. BM = baseline measurement FM = Final measurements with questionnaires, performed at the UMCU. Q = online questionnaire Q + M = measurement with questionnaires and physical measurements, performed at the UMCU

To evaluate changes in social functioning, and mental and physical health patients will receive a series of four online surveys. They will be invited before and after the intervention period to the UMCU for the surveys and physical measurements and a third time for only the surveys at the final measurement at the 21th month of the study. Mental health workers will receive one online questionnaire at baseline (Table 1).

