### Mental health worker

#### Primary outcome

##### Physical activity and lifestyle habits

The primary outcome for the mental health worker is their physical activity and lifestyle habits. The IPAQ-SF and the Dutch Healthy Diet Index will be conducted. The Dutch Healthy Diet Index is a screener for dietary quality based on Dutch and international nutrition guidelines and assesses 15 components of the Dutch dietary guidelines [51]. They will also be asked for their smoking status, drinking habits, length, and weight.

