### Data analysis

The primary analysis in this study evaluates if the Muva intervention improves social functioning in comparison to care as usual. This will be analyzed with a mixed-effects linear regression model taking into account clustering of outcome measurements within individuals and centers using random effects and possible confounding factors age, gender and diagnostic subgroups using fixed effects. In addition, we will include lifestyle habits and character traits of the mental health worker as dependent variables to analyze the association between the mental health workers’ characteristics and the outcome social functioning.

Modified intention-to-treat analysis will be done, but if patients move to a team of the supported housing organization without the Muva intervention or rehabilitation care stops within 3 months of intervention, patients will be analyzed in the control group since they will no longer receive the Muva intervention. Patients that drop out from the study, will be analyzed in the group they participated in.

Sensitivity analysis will be performed on cluster, attendance at intervention activities, and medication changes. Dropout analysis will be performed. Analysis will be done in IBM SPSS statistics 25 and R version 4.0.4, using a 95% confidence interval (*p* < 0.05).

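### Worker lifestyle and personality are entered as dependent variables where they must be explanatory; once corrected, the model gives the stated association but cannot show whether some workers make Muva more effective

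*Protocol article*

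**What the plan says.** The Data analysis section first defines the primary analysis: a "mixed-effects linear regression model taking into account clustering of outcome measurements within individuals and centers using random effects", with age, gender and diagnostic subgroup as fixed effects. It then adds that the trial will "include lifestyle habits and character traits of the mental health worker as dependent variables", and gives the purpose: "to analyze the association between the mental health workers’ characteristics and the outcome social functioning". It names no trait-by-intervention term and no worker-level random effect.

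The Objectives section states the aim in the same terms: "we will examine if the lifestyle habits and/or personality type of the mental health worker are associated with the outcomes". The hypothesis there is that "mental health workers with healthier lifestyles and a conscious personality type can contribute more to an active and healthy lifestyle of their patients". The Discussion repeats the hypothesis and promises to look for a correlation. Its closing paragraph hopes for insight into the worker's role in physical activity interventions.

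On measurement, the text under Table 1 says "Mental health workers will receive one online questionnaire at baseline", and Table 3 agrees. The section on the mental health worker nevertheless says "The primary outcome for the mental health worker is their physical activity and lifestyle habits".

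**The concern.** A dependent variable is what a model explains. Taken at its word, the plan would treat baseline worker traits as responses to patient scores collected later, while calling those scores the outcome. The sentence cannot be carried out as written.

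Correcting the word leaves two limits. First, a trait main effect pools control and intervention periods. It shows whether patients of certain workers score higher overall, not whether those workers get more out of Muva. Patients are not randomized to workers, so the coefficient also absorbs stable differences in case mix. Second, traits vary between workers, but the named random effects are for individuals and centers only. Patients who share a key worker would count as independent information about that worker's traits.

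At stake is what the trial can say about the worker's role. This is a supplementary question, separate from the primary comparison of Muva with care as usual.

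**Working it through.** **The plan's own figure.** The only design figure is the power of 0.93 for the primary comparison (Sample size), and this point does not depend on it. Across 64 analytic variants of the design, power ran from 0.28 to 1.00, with 9 variants within 2 points of 0.93. Table 1 and the simulation model are not shown, so the figure is neither confirmed nor refuted.

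**Step 1: the role of the variables.** The sentence calls worker traits dependent and social functioning the outcome. Both cannot hold in a model meant to explain social functioning. Since the traits are recorded once, at baseline, explanatory is the only workable role.

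**Step 2: what a main effect captures.** Let a trait w have slope b in all periods and an extra slope g under Muva. If the interaction is left out, the trait coefficient is about b + p × g, where p is the share of occasions that are exposed.

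Inputs from the Sample size section: 100 patients, seven time points, SD 9, intra-cluster correlation 0.1, correlation 0.8 (read here as within-person), effect 3 points. The variance of 81 then splits into 8.1 (cluster), 56.7 (patient) and 16.2 (residual).

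Assumed: 25 patients in each of four clusters; crossovers after the first, second and third occasions, with one cluster never crossing; an immediate effect; no dropout; one independent standardized trait score per patient; cluster and period fixed effects; known variance components.

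- Exposed share: (6 + 5 + 4) / (4 × 7) = 15/28 = 0.54. With eight occasions it would be 15/32 = 0.47.
- Purely prognostic trait (b = 1.5, g = 0): expected coefficient 1.50.
- Pure moderator (b = 0, g = 3): expected coefficient 3 × 15/28 = 1.61.

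Results of 1,000 simulated trials per scenario:

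| Scenario | Trait coefficient, main effect only (rejection) | Interaction coefficient when added (rejection) |
|---|---|---|
| Prognostic only | 1.50 (48%) | -0.02 (5.5%) |
| Moderator only | 1.61 (54%) | 2.98 (100%) |

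The main-effect model cannot tell the two apart; the interaction can. The effect sizes were chosen for illustration.

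**Step 3: precision of the two terms, same assumptions.**

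- Trait main effect: variance about (56.7 + 16.2/7)/100 = 0.590, SE about 0.77 per SD of trait.
- Interaction, from within-patient contrasts: k(7 - k)/7 for k = 6, 5, 4 exposed occasions sums to 0.857 + 1.429 + 1.714 = 4.00. Variance is 16.2/(25 × 4.00) = 0.162, SE 0.40 per SD.

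An interaction is usually the less precise term. Here it is not, because within-person correlation is high and every patient is assumed to respond alike for a given trait value. Variation between patients or workers in response to Muva would widen the interaction's interval, so the favourable ordering should not be relied on.

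**Step 4: the missing worker level.** If k patients share a worker and their scores correlate by r beyond the center effect, the SE of the trait main effect should be larger by the square root of 1 + (k - 1)r. Neither value is in the article. Assuming k from 2 to 5 and r from 0.05 to 0.2, the factor runs from √1.05 = 1.02 to √1.8 = 1.34. With one patient per worker it is 1.

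**The case against.** The strongest reply is that the sentence corrects itself. It names social functioning as the outcome, so a reader will substitute independent for dependent. The corrected model then delivers what is promised, because the Objectives, Data analysis and Discussion sections speak only of association or correlation. That stands.

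A reader might go further and infer that the trial's stated worker question is answered with the wrong estimate because no interaction is planned. The documents do not support this. The hypothesis concerns what workers contribute to patients' active lifestyle, not the size of the Muva effect. Workers can make that contribution under usual care too, since at least weekly guidance meetings are standard. The nearest wording to effect modification is the Discussion's closing hope, which is no analysis objective.

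It also stands that a condensed article may leave worker-level random effects to the full protocol or SAP, that patients per worker are not given, and that the analysis is introduced as an addition and may already be separate from the primary model. An interaction does not remove all confounding: it takes out stable case-mix differences in patients seen before and after crossover, but not differences in how case mix responds to Muva.

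Finally, calling baseline habits the worker's primary outcome is loose, but no analysis of change in workers is promised, so nothing is misestimated.

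The reply does not rescue the printed word, and it does not make a pooled main effect informative about whether some workers make Muva more effective.

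**Conclusion.** The stated role of the worker variables is wrong and should be corrected. It is evidently a slip, and it touches a supplementary analysis only.

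Beyond that, the planned terms suit the declared association but not the question that the hypothesis and the Discussion suggest is of interest: whether such workers make Muva more effective. In the illustration, a pure moderator shows up in the main effect at about half its slope (0.54, or 0.47 with eight occasions) and looks like a prognostic trait. Those shares rest on an assumed schedule and on a trait that acts only under Muva, which the protocol does not claim.

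The omitted worker level would overstate precision only if patients share a key worker. The size is unknown; the range of 1.02 to 1.34 in the standard error is assumed.

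The interaction and the worker random effect are therefore inexpensive improvements, not the repair of a broken promise.

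**What to change.** 1. In the Data analysis section, change dependent to explanatory.
2. State that this is a separate secondary model: SFS as outcome; worker trait, intervention and period as fixed effects; random effects for worker and person, keeping the planned center clustering.
3. Report the trait main effect as the stated association. Add a trait-by-intervention term, labelled exploratory, for conscientiousness and one prespecified lifestyle measure.
4. As a wording correction only, describe the worker's habits as a baseline characteristic and not as a primary outcome.

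The cost is a few words and one model on data already being collected. The downside is precision: the trial was sized for the treatment comparison, and an interaction is in general estimated less precisely than a main effect. Its interval should be reported, and an inconclusive result should not be read as evidence that workers do not matter.

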To improve social functioning by promoting physical activity in the treatment and daily life of people with SMI, it is important to lower these barriers. Mental health workers may have an important role in overcoming these barriers. They are responsible for the personal guidance in the daily living environment of people with SMI, for example, those receiving support from a supported housing organization. These workers are in close contact with the patient and could facilitate a supportive environment for making healthy lifestyle choices [25], set a good example, motivate the patient, provide social support, help with planning physical activities, and might thus potentially be of great value in overcoming barriers and to help patients with becoming physically more active. Previous research [26] showed that a lifestyle intervention including staff participation indeed improved physical activity and social functioning in hospitalized patients with SMI.

Moreover, the lifestyle and personality of the health care worker might play a role in their capacity to help patients overcome barriers to physical activity. Previous research in general health care showed that healthier lifestyle habits of the health care professional are associated with lifestyle counseling and referring practices to lifestyle interventions [27–30]. In addition, it was found that mental health workers, who worked in a supported housing organization, achieved the best psychiatric rehabilitation outcomes such as self-reliance in patients when they scored high on the personality trait ‘conscientiousness’ [31]. The authors suggested that conscious care planning is essential for the recovery process and that the mental health worker plays a key role in the recovery process [31]. However, it remains unknown if the lifestyle and personality type of the mental health worker matters for promoting physical activity in people with SMI.

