## Discussion

This trial is innovative since it aims to improve social functioning by promoting physical activity by focusing on lowering barriers for people with SMI to becoming physically active through the active involvement of the mental health worker, supporting lifestyle courses, and a medication review. Through this strategy, we aim to increase participation and motivation. Second, we will use the Muva serious game that is specifically designed for people with SMI and their mental health workers to support physical activity goals setting and to motivate participants to reach their goals. Third, the intervention will not only target the patient but also the mental health worker since they are an important factor in the environment of the patient and could facilitate a supportive environment for becoming physically active. We hypothesize that key workers with healthier lifestyles and a conscious personality type can contribute more to an active lifestyle of their patients and we will analyze if there is indeed a correlation. Fourth, a unique element of this trial is that we will investigate the posture and movement of the patient extensively with movement sequencing in gait with a real-time video camera and marker less motion capture and the Sint Hans Rating Scale to research movement disturbances that can form barriers to start and continue exercising and form risks for injuries for people with SMI. Fifth, we will investigate implementation barriers and facilitators and will contribute to the urgently needed evidence on translating evidence from physical activity intervention randomized controlled trials into real-life practice [6, 7, 37]. With these strategies, we will complement previous knowledge on physical activity interventions in people with SMI.

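### The worker hypothesis is about patients' physical activity, but the one worker analysis the protocol specifies has social functioning as its outcome

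*Protocol article*

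**What the plan says.** The worker question appears in four places in the protocol article.

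- **Background** names the gap in knowledge: "it remains unknown if the lifestyle and personality type of the mental health worker matters for promoting physical activity in people with SMI".
- **Objectives** gives a broad aim, namely whether "lifestyle habits and/or personality type of the mental health worker are associated with the outcomes", followed by a specific hypothesis: "mental health workers with healthier lifestyles and a conscious personality type can contribute more to an active and healthy lifestyle of their patients".
- **Discussion** repeats the hypothesis and commits to testing it: such workers "can contribute more to an active lifestyle of their patients and we will analyze if there is indeed a correlation".
- **Data analysis** is the only place that fixes a worker analysis. It says "we will include lifestyle habits and character traits of the mental health worker as dependent variables to analyze the association" between the workers' "characteristics and the outcome social functioning".

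On the data side, Table 3 schedules the patient IPAQ-SF at the UMCU visits, which in the intervention groups fall before the start of the intervention and 12 months after it. Workers complete the IPAQ-SF, the Dutch Healthy Diet Index and the NEO five-factor inventory once, at baseline. The SFS is in every online questionnaire; the patient IPAQ-SF is not.

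**The concern.** The hypothesis and the promised correlation have patient activity as their endpoint. The specified model has social functioning. These are different questions, and a result on one does not settle the other.

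The Background section treats physical activity as a route to better social functioning. If worker traits act on activity first, their association with the SFS will be weaker than their association with activity, so a null SFS result says little about the hypothesis. A positive SFS result would not confirm it either, because a conscientious worker may improve functioning through good care planning in general. The Background section itself cites earlier work linking conscientiousness to rehabilitation outcomes such as self-reliance.

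At stake is a named secondary objective. The comparison of the intervention with usual care is not touched.

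**Working it through.** **1. The passages side by side**

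| Section | Endpoint of the worker question |
|---|---|
| Background | promotion of patients' physical activity |
| Objectives, aim | the outcomes, plural and unspecified |
| Objectives, hypothesis | patients' active and healthy lifestyle |
| Discussion | patients' active lifestyle, correlation to be analysed |
| Data analysis | social functioning |

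The model in the last row fits the second row in part, since the SFS is one of the outcomes. It does not fit the first, third or fourth. The data for those rows are planned: patient IPAQ-SF at two visits, and worker variables at baseline.

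**2. The role of the worker variables**

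The same sentence calls worker habits and traits dependent variables, yet social functioning is the outcome. They are explanatory variables in that model.

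**3. Illustration of what the choice of endpoint can do to power**

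The protocol states no power for the worker analysis. Its figure of 0.93 concerns the intervention effect on the SFS and is not used here.

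Inputs from the protocol: 100 patients, 30% dropout, four areas of which three receive the intervention, and a 5% significance level (taken as two-sided).

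Assumptions not in the protocol: equal areas of 25 patients, independent patients, one SFS value per patient, and all correlations.

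- Sample for a direct IPAQ-SF test: 3 × 25 = 75, and 75 × 0.7 = 52.5, taken as 52. Sample for the SFS test: 70 to 100.
- Formula: δ = atanh(r) × √(n − 3); power = Φ(δ − 1.96) + Φ(−δ − 1.96).

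Direct test on activity:

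| r | n | δ | Power |
|---|---|---|---|
| 0.1 | 52 | 0.70 | 0.11 |
| 0.2 | 52 | 1.42 | 0.29 |
| 0.3 | 52 | 2.17 | 0.58 |
| 0.4 | 52 | 2.97 | 0.84 |
| 0.3 | 40 | 1.88 | 0.47 |

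The n = 40 row shows the effect of further loss through missed hospital visits.

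Test on the SFS if traits act only through activity, so that the correlation is the product of the two links:

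- 0.3 × 0.3 = 0.09: power 0.11 at n = 70 and 0.14 at n = 100.
- Across trait–activity 0.3 to 0.4 and activity–SFS 0.2 to 0.5, the product runs from 0.06 to 0.20 and power from 0.08 (0.06, n = 70) to 0.51 (0.20, n = 100).

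Test on the SFS if a direct path of 0.10 to 0.20 is added to the 0.09:

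- r = 0.19: power 0.35 at n = 70 and 0.47 at n = 100.
- r = 0.29: power 0.69 at n = 70 and 0.84 at n = 100.

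So which test has more power depends on assumptions that the protocol cannot settle. What does not depend on them is that only the first test addresses activity.

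**The case against.** The worker sentence extends the primary model, so it naturally names the primary outcome, and it does not say that nothing else will be tested. The article gives no separate model for any secondary outcome, and a condensed article may leave that to the full plan. Objectives speaks of outcomes in the plural, and Discussion announces the activity correlation, so the intention to test it is on record. The SFS model also answers part of the stated aim.

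Much of this stands. A reader might infer that the activity question has been abandoned, or that a null SFS result would be misread as refuting the hypothesis. The documents support neither: they declare the intention, and they do not say how a null result would be interpreted. The power illustration is also open to attack. A path from worker traits to functioning that bypasses activity is plausible on the protocol's own Background section, the SFS is measured repeatedly, and 52 is a favourable count.

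What does not stand is the appeal to silence. The article does not leave the endpoint of the worker analysis open; it names one, and that one differs from the endpoint of the hypothesis it states and promises to examine.

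**Conclusion.** The mismatch holds as a matter of text. As specified, the worker analysis addresses the broad aim in Objectives but does not test the activity hypothesis stated in Objectives and repeated in Discussion. The labelling of worker traits as dependent variables is a separate error in the same sentence.

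No size can be given from the documents. The power figures are illustrative: they rest on assumed correlations, and the low SFS figures also need the absence of any direct path from traits to functioning. The direct IPAQ-SF test is no guarantee of an answer either; at r = 0.2 with 52 patients its power is about 0.29. Patients who share a worker would lower the figures further. The case for change is therefore that the analysis should match the question, not that one test is sure to succeed. It is a worthwhile correction to a secondary objective, with no bearing on the primary conclusion.

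**What to change.** In Data analysis:

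- Name patient physical activity as the outcome for the worker hypothesis: IPAQ-SF about 12 months after the start of the intervention, adjusted for the pre-start value. Other ways of using the two values are possible; the point is to fix one in advance.
- Enter worker lifestyle and personality as explanatory variables, and correct the term in the existing sentence.
- Allow for patients who share a worker, where this occurs.
- Keep the SFS model as a separate association, and state that neither a null nor a positive SFS result is by itself evidence on whether workers promote patient activity.

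The cost is one extra model, with no new visit or instrument. The drawback is a smaller and self-reported dataset: the IPAQ-SF is taken only at the UMCU visits, which the Discussion expects some patients to miss. The stated visit timing covers the intervention groups; whether the control area has such visits cannot be told from the text, because Table 1 is not shown.

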All teams of the supported housing organization (*n* = 30) will be invited to participate in the study. Teams in four different areas of Utrecht will be chosen to participate to prevent spillover effects and contamination since teams work closely together in these areas. Every area will form a cluster. Three clusters will start the intervention in a stepped wedged order, within intervals of three months, and one cluster will remain the control group during the study period (Table 1). To determine which area is allocated to which cluster to start the intervention, a simple randomization method is performed by drawing lots. Hence, randomization is done at cluster level and not at patient level. Randomization at patient level is not possible since teams deliver equal rehabilitation care to the patients of their team. Given the stepped wedge design and the vulnerable patient group, for whom continuity of research team is desired, participants and the research team know when each cluster will crossover from unexposed to the exposed period, also reducing the possibility of drop-out. Nevertheless, to reduce rater bias the final measurement at the 21th month of the study, will be performed blind to the intervention exposure duration (Table 1).

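### The modified intention-to-treat rule analyses some Muva patients as control because of an event after randomisation, so the primary comparison is not the randomised one

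*Protocol article*

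**What the plan says.** All of the relevant text is in the protocol article.

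- Study design and setting: four areas form the clusters. Three start Muva at three-month intervals and one stays in the control condition throughout; "randomization is done at cluster level and not at patient level".
- Data analysis, aim: "The primary analysis in this study evaluates if the Muva intervention improves social functioning in comparison to care as usual", using a "mixed-effects linear regression model taking into account clustering of outcome measurements within individuals and centers using random effects".
- Data analysis, analysis set: "Modified intention-to-treat analysis will be done". The exception applies "if patients move to a team of the supported housing organization without the Muva intervention or rehabilitation care stops within 3 months of intervention"; in that case "patients will be analyzed in the control group since they will no longer receive the Muva intervention".
- Data analysis, study dropout: "Patients that drop out from the study, will be analyzed in the group they participated in".
- Data analysis, sensitivity: "Sensitivity analysis will be performed on cluster, attendance at intervention activities, and medication changes".

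The article gives no other rule for assigning patients or measurements to a condition in the primary analysis.

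**The concern.** The stated reason for recoding is the treatment received. The triggers, a change of team or an end of care, occur after the area has been allocated and has crossed over. The rule also works in one direction. A patient with the same event in a control period stays in control, while the exposed patient is taken out of intervention and added to control. Intervention data lose their early leavers; control data keep their own and gain the others.

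If leaving is related to the outcome, this produces a difference even when Muva does nothing. A link is plausible: the organisation aims at independence, its patients range from ambulatory care to 24-hour houses, and the SFS domains kept for the primary outcome include two on independence. A patient who leaves within 3 months may also already have had the activity check and the medication review, which the article places at the start of the intervention. Coding that patient as control puts exposed data into the control condition.

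**Working it through.** **Plan's own figure.** The article gives no number of patients to be recoded and no leaving rate, so there is nothing to reproduce on this point. Its power of 0.93 can be reached under one reading of its inputs (0.940 with 7 visits and 100 patients, effect growing linearly to 3 points at 12 months, crossover at months 3, 6 and 9). Nothing below depends on it.

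**Inputs from the article.** 100 patients, four areas, SD 9 and a target of 3 SFS points (Sample size; Study design and setting).

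**Assumptions.** 25 patients per area; true effect zero; leaving at the same rate in every area whatever its condition; SFS shifted after leaving by 4.5 points (half an SD) or 9 points (one SD); leavers still measured; crossover at months 3/6/9 or 6/9/12, because Table 1 is not shown.

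**Hand check at the first step.** One area is exposed (25 patients) and three are not (75). Let 5% of all patients leave in that quarter and fall by 4.5 points.

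- As randomised: exposed mean shift 0.05 × (−4.5) = −0.225; control mean shift the same; difference 0.
- Recoded: the 25 × 0.05 = 1.25 exposed leavers join the 75 × 0.05 = 3.75 control leavers. Exposed shift is 0. Control shift is (1.25 + 3.75) × (−4.5) / (75 + 1.25) = −22.5 / 76.25 = −0.295. Difference **+0.30**.
- With a 9-point fall: −45 / 76.25 = −0.59, so **+0.59**. With a rise instead of a fall the sign reverses.

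**Whole schedule, 3-month window, two-way (person and period) model.** The bias is proportional to the shift, so the last column doubles the middle one.

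| Leaving per 3 months | Bias, 4.5-point fall | Bias, 9-point fall (×2) |
|---|---|---|
| 1% | +0.08 to +0.10 | +0.16 to +0.20 |
| 2% | +0.15 to +0.20 | +0.30 to +0.40 |
| 5% | +0.29 to +0.41 | +0.58 to +0.82 |

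**Monte Carlo check** (1,500 runs per setting, 8 visits, crossover at 3/6/9, all post-crossover visits of a leaver recoded). At 5%, about 3.4 of 75 intervention patients are recoded, and the mean estimate is +0.33 (4.5-point fall) and +0.60 (9-point fall). At 10%, about 6 are recoded, giving +0.43 and +0.87. If leavers improve by 4.5 points, the bias is −0.30 at 5% and −0.44 at 10%. If leaving is uninformative it is about 0. As-randomised coding stays between −0.01 and +0.03 throughout.

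**If moves at any time are recoded.** Monte Carlo at 2% to 4% per 3 months (about 7 to 13 recoded) gives +0.41 to +0.64 for a 4.5-point fall and +0.80 to +1.27 for 9. At 5%, the 4.5-point case runs from about +0.56 to +1.88. The result depends on whether all post-crossover visits or only those after the move are recoded, and on whether patients who moved before crossover count.

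**With a true effect of 3.0.** Across the Monte Carlo settings (up to 20% leaving in the window, or up to 4% per 3 months at any time), recoding gives 2.2 to 4.1 depending on who leaves. As-randomised coding gives 2.75 to 2.96.

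**The case against.** The best defence is that the rule is narrow and its effect unknown. Care stopping counts only within 3 months of intervention, and the same limit may cover moves. Few patients may qualify: at 1% per quarter the bias is about 0.1 to 0.2 points. No section says why patients move or lose care, so a link with the outcome is plausible but not documented. The scenarios also assume that leavers keep completing the SFS; if their data end when care ends, recoding touches few measurements. All of this stands, and it limits the size of the problem. It does not restore the randomised comparison.

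Four stronger readings are tempting and are not supported.

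- *Everyone who ever leaves is recoded.* The text limits stopping of care to 3 months and is unclear on moves.
- *The 30% anticipated dropout is the number recoded.* Study dropouts are kept in their own group, so that figure is not the trigger.
- *The rule contradicts the dropout sentence.* Leaving care or changing team is a different event from leaving the study. A patient who does both falls under both sentences with no stated precedence, which is a gap and not a contradiction.
- *The rule favours Muva.* The direction depends on who leaves, which the article does not tell us.

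**Conclusion.** The point holds in this limited form. As written, the primary analysis classifies some exposed patients by treatment received, on a post-randomisation event and in one direction only, and the listed sensitivity analyses include no as-randomised check. Two things are left unclear: whether the 3-month limit applies to moves, and whether control group means control-condition time or the area that never crosses over.

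The size is known only by scenario. Under the assumptions listed, with a 3-month window and 1% to 5% leaving per 3 months, the bias is about 0.1 to 0.4 SFS points for a 4.5-point change and about 0.2 to 0.8 for a 9-point change (about 0.9 at 10%). Against the 3-point target, 0.4 is 13% and 0.8 is 27%. It is positive if leavers worsen, negative if they improve and about zero if leaving is uninformative. Any-time recoding would make it larger, but no single figure for that is defensible. Simulated rejection rates are not used, because the assumed shift also disturbs the variance model.

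**What to change.** In the primary analysis, code each available measurement by the scheduled exposure, at that calendar time, of the area where the patient was recruited, whatever moves or stops of care follow. Keep the recoded version as a labelled sensitivity analysis. For that version, state whether the 3-month limit covers moves, which visits are recoded and to what, and which sentence governs a patient who both stops care and leaves the study.

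For measurements already planned this is a change of wording. It has two costs. The first is dilution: if 10% get no benefit, 3.0 × 0.90 = 2.7, and the scenarios run gave 2.75 to 2.96, so roughly 2.7 to 2.95. Heavier leaving dilutes more: at 5% per 3 months from the start, 0.95⁴ = 0.81 remain at month 12, and 3.0 × 0.81 = 2.4 if leavers lose all benefit at once. This is the effect of introducing Muva in an area, which suits a pragmatic trial. The second is that measurements missing after care stops have to be handled under the mixed model's missing-data assumption, unless leavers continue to be followed.
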